# Transferability of a 10-week remotely delivered Virtual Physical Activity Seated Exercise (V-PASE) program on post-stroke functional mobility: study protocol for a multisite randomized controlled trial

**DOI:** 10.1186/s13063-026-09523-8

**Published:** 2026-02-06

**Keywords:** Stroke, Videoconferencing, Rehabilitation, Mobility, Balance, Seated exercise

## Abstract

**Background:**

Seated exercises may reduce the need for in-person support during home-based exercise programs in people with balance impairments. However, it is uncertain if these exercises can transfer to improved lower extremity function and mobility. Thus, the objective is to investigate the effects of a remotely delivered 10-week seated exercise intervention on functional mobility, compared with control, in individuals living with a chronic stroke who have balance impairments.

**Methods:**

The study is a multi-site, assessor blinded, randomized controlled trial that will recruit across five provinces in Canada using the CanStroke Recovery Trials platform. A total of 100 adults living with a chronic stroke (≥ 6 months post-stroke) and mobility impairment (using a walking aid) will be recruited. Participants will be randomized (1:1) to the 10-week Virtual Physical Activity Seated Exercise (V-PASE) or control group. All exercise sessions will be delivered one-on-one through videoconferencing by a trained instructor. Sessions will be 60 min in duration and completed 3 times/week at a moderate intensity (40%–60% Heart Rate Reserve). The primary outcome measure is the 30s Sit-To-Stand score at the end of the 10-week intervention. Secondary outcome measures will be mobility, balance, quality of life, stroke-related quality of life, cognition, fatigue, anxiety, depression, and blood profiles (glucose and lipids).

**Discussion:**

Exercises completed in a chair have the potential to transfer to improved functional mobility in people with balance impairments, such as individuals with stroke. The stability of the seated position may improve safety during home-based exercises and thus increase participation.

**Trial registration:**

ClinicalTrials.gov NCT05724823. Registered on February 13th, 2023.

**Supplementary Information:**

The online version contains supplementary material available at 10.1186/s13063-026-09523-8.

## Background

One in four people aged over 25 will experience a stroke over their lifetime [1] and up to 46% will live with a stroke-related disability [2]. Disability manifests as a variety of physical and psychological impairments, with impaired mobility the most reported (58% of people with stroke) long-term consequence after stroke [3]. Improving mobility is an important priority for individuals living with stroke [4, 5]. However, functional mobility (balance and walking ability) can deteriorate over time in people with moderate severity strokes [6] and could result in reduced independence in daily activities [7] and an increased risk of falls [8].

Regular physical activity can improve mobility [9] and modifiable risk factors (cardiovascular and metabolic risk factors) for recurrent stroke [10]. Interventions that incorporate circuit training, aerobic training, or multimodal training have been found to improve balance and mobility outcomes in people with stroke [11–13]. However, people with stroke often report impaired function, fear of falling, and limited access to services and community programs as barriers to engaging in physical activity [14–16]. This reinforces the need for safe home-based programs that can be delivered remotely to increase physical activity engagement and improve mobility after stroke.

Home-based exercise programs have been found to produce similar improvements in mobility and balance in people with acute and chronic stroke, when compared with exercises delivered at hospital or community centres [17]. When delivered remotely through videoconferencing, home-based exercise interventions are also reported to improve mobility [18] and perceived fitness and function [19] after stroke. Galloway et al. [19] reported high feasibility of a remotely delivered exercise intervention, with 95% of participants reporting high usability and satisfaction. However, a survey of physiotherapists (*n* = 75) working in predominately outpatient or community settings found 70% (*n* = 53) believed they could not treat mobility or balance effectively over videoconferencing, and 53% believed that participant safety was a barrier to using videoconferencing to provide treatment [20]. In addition, a barrier to participation in remotely delivered exercise trials is the typical requirement for someone to be at home to assist, with up to 39% of stroke survivors being ineligible due to the lack of available in-person assistance [19, 21]. Thus, improving the stability of the exercising participant through seated exercises may be a safer alternative to traditional walking exercises when delivered remotely, and remove the need for in-person physical assistance.

In-person seated exercise programs have been shown to improve balance and mobility outcomes in people living with stroke [22]. In a recent case report conducted by our team, we found that two weeks of seated exercises delivered through videoconferencing resulted in clinically meaningful changes in balance, lower extremity strength, walking speed, and cardiorespiratory fitness in a person living with a chronic stroke [23]. In addition, the participant experienced no adverse events or falls. Our case report highlights the potential for seated exercises to be a safe alternative to traditional standing and walking exercise for home-based programs and provides the basis for this clinical trial. Thus, the objective is to determine the effects of a remotely delivered 10-week seated exercise intervention on functional standing and walking mobility in people with a chronic stroke and mobility impairment.

## Methods

### Study design

This study is an assessor-blinded, parallel-group, multi-site randomized controlled trial (Fig. 1). Participants will be randomized 1:1 to a 10-week Virtual Physical Activity Seated Exercise group (V-PASE) or a control group continuing with usual care (Control) after completion of the baseline assessment. The study will be delivered in real-time through videoconferencing services. Assessors will be blinded to the group assignments. The study protocol (Version 9, April 5th, 2024) is registered with clinicaltrials.gov (NCT05724823) and adheres to the Standard Protocol Items: Recommendations for Intervention Trials [24] and CONSORT [25] guidelines.

**Fig. 1 Fig1:**
[figure not shown]
Flow diagram of assessor-blinded, multi-site randomized controlled trial

### Study setting

The study will recruit community-dwelling people living with chronic stroke from sites in British Columbia, Saskatchewan, Manitoba, Ontario, and Nova Scotia that are associated with the Canstroke Recovery Trials Platform (https://canadianstroke.ca/). Recruitment will be conducted through affiliated hospitals and outpatient centres of site investigators and through local community and stroke recovery programs. The central research team at GF Strong Rehabilitation Centre (Vancouver, BC) will support individual sites on the study setup (including ethics), training, and processes. However, each site will independently recruit, consent, screen, enrol, schedule (assessments, exercise sessions, and blood work), input and manage data, and follow up participants. The central team will train staff at each site on the study protocols and will conduct fidelity assessments at regular intervals during the study.

### Population

The project will recruit community-dwelling adults (where adults are defined by the province) living with a chronic stroke (≥ 6 months). People with stroke will be included if they (1) have a mobility impairment (i.e., uses a walking aid in outdoor or large indoor spaces), (2) can stand up from a sitting position (with or without support or assistive devices), (3) have access to the internet and a device with a video camera, and (4) are able to communicate in English. Exceptions will be made to the English language criteria if assessors and instructors can translate for the participant.

People with stroke will be excluded if they (1) are participating in a formal exercise program or engaging in physical activity that exceeds 150 minutes/week moderate-intensity physical activity, (2) are enrolled in another exercise trial or rehabilitation services (e.g., lower extremity physiotherapy) that may affect the outcomes of the study, (3), have severe loss of hearing, speech, or vision, or (4) have a serious comorbid condition or have been diagnosed with a condition that could affect participation (e.g., leg amputation, Parkinson’s disease, active cancer). In addition, a helper (e.g., caregiver, family member, or friend) is required to attend in-person during outcome assessments only, but they are not required during exercise sessions.

### Randomization

Randomization will be completed through an online third-party service (Diamind Solutions) following completion of the baseline assessment. Enrolled participants will be randomized within site, by coordinators, to the V-PASE or control group. Group allocation will be blinded for assessors only, and assessors will be instructed to refrain from asking the participant about study details. Randomization will be conducted using the Minimum Sufficient Balance (MSB) [26] algorithm that ensures balanced allocation across specific stratification factors. Participants will be stratified based on site, age (continuous variable; years), sex (categorical; male, female), time post-stroke (continuous; months), Modified Rankin Scale (continuous; 0–5), Fatigue Assessment Scale (continuous; 10–50), and walking speed calculated from the Timed Up and Go (continuous; cm/s).

The MSB algorithm will detect any imbalances in allocations across groups and will adjust the probability of assignment according to the following parameters. The first 10 participants will have a 50% (50/50) probability of being assigned to the V-PASE group or the control group. If an imbalance is detected in the next 80% of participants, the algorithm will adjust the probability assignment from 50/50 to 70/30. In the final 20% of participants, the probability will be adjusted to 90/10 to correct any imbalances.

### Initial setup session and safety considerations

A 60-minute setup session will be completed by the trained instructor with the participant via videoconferencing services prior to starting the seated exercise intervention. Prior to the setup session, participants will be mailed an equipment package that contains one Fitbit Versa 4 smartwatch (Versa 4, Fitbit, Inc, Canada), a Samsung Galaxy Tab A7 tablet, two adjustable weighted cuffs (1 lb each), a V-PASE exercise manual containing pictures and descriptions of the exercises, and a Fitbit Versa 4 and Samsung Galaxy Tab A7 user manual. During the setup session, the instructor will show the participant how to use the equipment, will conduct a safety check of the participant's environment (visual), and will complete a demonstration of the exercises. The instructor will perform each exercise with the participant and ensure exercises are performed safely and correctly. The instructor can modify exercises if a participant reports any discomfort or pain during an exercise.

The participant will be instructed to wear the Fitbit watch on the non-paretic wrist during the setup session and exercise sessions. In the setup session, the instructor will ask the participant to report their current heart rate after 10 minutes of seated rest. After each session, the participant will be asked to sync the Fitbit watch with the Fitbit app on the Samsung Tablet provided so that a data accuracy check can be completed by the site coordinator.

### Intervention

Seated exercises will be delivered one-on-one remotely through videoconferencing services three times a week by a trained instructor with a degree in kinesiology, physical therapy, or occupational therapy and experience in delivering exercise interventions. The intervention group (V-PASE) will complete a total of 30 sessions, and the control group will continue with usual care. Usual care may involve participating in recreational programs or physical activity that does not exceed 150 minutes per week of moderate-intensity physical activity or upper extremity rehabilitation. The control group will receive a 2-week (6 sessions) seated exercise intervention on completion of the post-intervention assessment to facilitate retention in the study.

Exercise sessions will be 60 minutes in duration and will include a 5-minute warm-up, 50 minutes of structured exercises, and a 5-minute cool-down. Twelve exercises (upper body, lower body, core) will be completed during the 50-minute structured exercise component that will focus on aerobic fitness, weight-bearing, strength training, agility, and coordination. Details of the twelve exercises are listed in Supplementary Table 1 and have also been described and published elsewhere [23].

Instructors will modify exercises according to participant function and will progress exercises by increasing the number of repetitions (e.g., 10 to 30 repetitions), sets (e.g., 3 to 5 sets), duration (e.g., 1 to 5 minutes), speed of movement, using weighted cuffs (1 lb each), and transitioning from mini-lifts to full sit-to-stands. Exercises will be completed in a sturdy chair and participants will be instructed to work at a moderate intensity of 40%–60% Heart Rate Reserve (HRR) [27]. To ensure a moderate intensity is maintained during sessions, priority will be placed on aerobic and lower extremity exercises as demonstrated in our case-report [23]. The instructor will ask the participant to report their heart rate (using the Fitbit Versa 4 watch) and perceived physical exertion (using the 0–10 Rating of Perceived exertion scale [RPE, 0 = rest, 10 = maximal]) at regular intervals in each session to ensure target intensity is achieved. At-home support from a helper (e.g., caregiver, family member) is not required during seated exercise sessions. However, instructors will conduct a safety check at the start of each session confirming the participant’s health, contact details, and location.

### Outcomes

Outcomes will be collected remotely through videoconferencing at baseline (T0) and immediately post-intervention (T10) (Table 1). Assessments will be conducted by a trained assessor who has a degree or qualification in physical therapy or occupational therapy. Assessors will be blinded to the participant group.

**Table 1 Tab1:** Schedule of baseline and post-intervention assessments

Timepoint	Baseline (T0)		Post-intervention (T10)	
Group	V-PASE	Control	V-PASE	Control
Demographics	x	x		
Primary outcome				
Modified 30 s Sit-To-Stand test	x	x	x	x
Secondary outcomes				
Fatigue Severity Scale	x	x	x	x
Activities-specific Balance Confidence Scale	x	x	x	x
Modified Fugl-Meyer – lower extremity	x	x	x	x
Tandem stance	x	x	x	x
Stroke Impact Scale	x	x	x	x
Timed Up and Go	x	x	x	x
EQ-5D-5L	x	x	x	x
PHQ-4	x	x	x	x
MoCA-BLIND	x	x	x	x
Blood profiles *HbA1c, fasting glucose, cholesterol (total, HDL, LDL), lipid, triglycerides*	x	x	x	x

*V-PASE* Virtual Physical Activity Seated Exercise, *EQ-5D-5L* EuroQol-5D-5L, *PHQ-4* Patient Health Questionnaire, *MoCA-BLIND* Montreal Cognitive Assessment BLIND, *HbA1c* hemoglobin A1c, *HDL* high-density lipoprotein, *LDL* low-density lipoprotein

Participant demographics will be collected at baseline (T0) and include age, sex, gender (using the Stanford Gender Questionnaire [28]), employment status, living arrangements, type of walking aid used, comorbidities (Functional comorbidity index [29]), medication, stroke profile (date, number of strokes, type of stroke, side affected, Modified Rankin Scale [30], adapted National Institute of Health Stroke Scale [motor arm, motor leg, limb ataxia, best language, dysarthria] [31, 32]), and fatigue (Fatigue Assessment Scale [33]).

### Primary outcome

The primary outcome will be functional mobility using the modified 30 second Sit-To-Stand (STS) [34] score immediately post-intervention (T10). The modified 30 s STS test allows participants the opportunity to use their arms if they are unable to complete a STS unassisted, providing a more appropriate assessment of lower extremity strength performance in lower functioning individuals [34]. Participants will be seated on a standard chair with armrests and will be asked to complete as many STS as possible within 30 s. One practice trial will be allowed prior to the assessment, and participants will be encouraged to perform the modified 30 s STS test without the use of arms. If a participant uses their arms during the modified 30 s STS test at baseline (T0), then at T10 they will first attempt a modified 30 s STS test without using arms, then perform the modified 30 s STS with use of their arms.

### Secondary outcomes

Balance and mobility will be measured by the Timed Up and Go (TUG) [35, 36] where participants will be asked to stand up from an armed chair, walk 3 m at a comfortable pace, and then return to the chair. One practice TUG will be completed prior to the timed assessment. Standing balance will be assessed by the tandem stance as reported in the Short Physical Performance Battery [37]. Participants will be timed (up to 10 s) to stand in three different positions: feet side-by-side, semi-tandem stance, and tandem stance. Motor impairment will be assessed using the modified Fugl-Meyer (lower extremity) that was adapted for videoconferencing [38, 39]. The modified Fugl-Meyer (lower extremity) includes four tasks that are completed in a seated position (flexor synergy, extensor synergy, combined synergies, coordination and speed) [38, 39].

Fatigue will be measured using the nine-question Fatigue Severity Scale, which assesses the impacts of fatigue over the last week using an 8-point Likert scale (0 = strongly disagree, 7 = strongly agree) [40]. Stroke-related quality of life will be assessed using the Stroke Impact Scale (SIS), which comprises 8 domains focusing on (1) activities of daily living, (2) communication, (3) emotion, (4) hand function, (5) memory, (6) mobility, (7) participation, and (8) strength [41]. Health-related quality of life will be assessed using the five-question EuroQol-5D-5L (mobility, self-care, usual activities, pain/discomfort, anxiety/depression), which also includes a visual analogue scale to record a participant’s self-rated health today (0% = worst health, 100% = best health) [42]. The Patient Health Questionnaire-4 (PHQ-4) will evaluate symptoms of anxiety and depression over the last 2 weeks using a 4-point Likert scale (0 = “Not at all”, 3 = “Nearly every day”) [43]. Balance confidence will be assessed with the Activities-specific Balance Confidence (ABC) scale that evaluates a participant’s confidence in performing 16 activities while maintaining standing balance [44]. As exercise can improve cognitive function after stroke [45], cognitive function will be measured using the Montreal Cognitive Assessment Scale BLIND (MoCA-BLIND) [46]. The MoCA BLIND was adapted for remote and telephone delivery by excluding the visual and drawing tasks yet still evaluating abstraction, attention, delayed recall, language, memory, and orientation. All questionnaires will be read aloud by the assessor and screenshared for participants to see, except for the MoCA-BLIND.

As exercise may improve cardiovascular and metabolic risk factors for stroke [47], blood biomarkers will include fasting glucose, Haemoglobin A1c (HbA1c), Low-Density Lipoprotein (LDL), High-Density Lipoprotein (HDL), total cholesterol, and triglycerides. Participants will be asked to fast for at least 12 hours before attending a local blood collection facility.

Adherence will be assessed by recording the percentage of sessions attended by participants and the intensity of exercise achieved (using HRR). Protocol deviations will be tracked. Safety will be monitored through the number of falls and adverse and serious adverse events reported. Serious adverse events will be defined as admission to acute care.

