### Data collection and monitoring

Data will be directly inputted into a database created using the Research Electronic Data capture (REDCap) system and housed on the University of British Columbia REDCap server. All data inputted into REDCap will be site-specific and de-identified except for participant demographics such as year of birth and sex. Each site will maintain access to site-specific data through REDCap. Site coordinators will meet weekly to discuss study progress, trial deviations, and recruitment strategies. Any unfavourable or unintended symptoms or events (e.g., pain or soreness from intervention, falls) that occur to participants during the trial will be reported as an adverse event in REDCap. All minor adverse events will be reported to the data safety monitoring board (DSMB) every 4 months and will be classified on severity and potential relatedness to the trial. Instructors will modify or stop exercises if minor adverse events occur during exercise sessions. Serious adverse events will be reported directly to the DSMB within 48 hours and according to site-specific ethics protocols.

A fidelity check will be completed for assessments and exercise sessions by the central team (primary coordinator) at regular intervals to ensure the study protocols are followed consistently across sites. The fidelity check will focus on how session expectations are communicated to participants, how sessions are managed, how exercises are progressed, ensuring participant safety, and ensuring a supportive environment for participants is created. Feedback will be provided immediately to assessors and instructors if any deviations to the protocol occur.

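### Serious adverse events are defined only by acute-care admission, so a death or disabling event without admission has no stated expedited route to the safety board

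*Protocol article*

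**What the plan says.** Safety is covered in two places in the Protocol article.

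The end of the Secondary outcomes section names the measures: "Safety will be monitored through the number of falls and adverse and serious adverse events reported". It then gives the definition: "Serious adverse events will be defined as admission to acute care". No word marks admission as an example or as one criterion among several.

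The Data collection and monitoring section sets out recording and reporting. Any untoward symptom or event in a participant, falls included, "will be reported as an adverse event in REDCap". Reports to the DSMB then follow two routes. The slower is "All minor adverse events will be reported to the data safety monitoring board (DSMB) every 4 months", and these events "will be classified on severity and potential relatedness to the trial". The faster is "Serious adverse events will be reported directly to the DSMB within 48 hours and according to site-specific ethics protocols".

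On the setting, the Intervention section states: "At-home support from a helper (e.g., caregiver, family member) is not required during seated exercise sessions".

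**The concern.** The definition turns on place of care, not on the outcome of the event. Admission is one common marker of seriousness, but some of the gravest events involve none. A person who dies at home is never admitted. A fall that leaves lasting disability may be handled by an emergency visit and discharge. The 48-hour report depends on the serious label alone, so a definition that is too narrow also narrows what the DSMB hears about quickly.

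Two things are at stake. One is timely oversight, in people with chronic stroke and impaired mobility who exercise at home with no helper required. The other is the reported count of serious adverse events, one of the trial's stated safety measures. The article's rationale relies on seated exercise being a safe option without in-person help, so readers will look at that count. The primary comparison on the 30 s Sit-To-Stand score is not affected.

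**Working it through.** No arithmetic applies beyond the two reporting clocks, and the plan states no safety figure to reproduce. The check is to take the definition and the routes as written and pass different kinds of event through them.

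Inputs:
- Serious means admission to acute care (Secondary outcomes).
- Serious events go to the DSMB within 48 hours (Data collection and monitoring).
- Minor events go to the DSMB every 4 months, graded for severity and relatedness (same section).
- All untoward events are entered in REDCap (same section); no DSMB deadline is attached to that entry.
- Falls are counted as a separate safety measure (Secondary outcomes).

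| Event | Serious as worded? | 48-hour DSMB report? | 4-monthly DSMB report? | Captured elsewhere? |
|---|---|---|---|---|
| Untoward event with acute-care admission | Yes | Yes | Not needed | REDCap |
| Death outside hospital | No | Not triggered | Only if called minor | REDCap |
| Life-threatening event, no admission | No | Not triggered | Only if called minor | REDCap |
| Disabling fall, no admission | No | Not triggered | Only if called minor | REDCap and fall count |
| Muscle soreness after exercise | No | No | Yes | REDCap |

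The first and last rows work as intended. The middle three do not.

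1. None of the three meets the single criterion, so none is serious and the 48-hour report is not triggered.
2. The article does not say that every event that is not serious is minor. Two readings remain. If such an event is filed as minor, it goes with the next 4-monthly report, so the wait is at most about one 4-month interval against 48 hours. If it is regarded as neither minor nor serious, no DSMB route is stated.
3. Severity grading does not close the gap. It is described for minor events, and no rule moves an event graded severe to the 48-hour route.
4. On either reading the event is absent from the serious-event count, though present among all adverse events.

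No other section of the article adds a criterion for seriousness or a separate expedited route for these events.

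**The case against.** The strongest reply is that this is a condensed article. It names a full protocol, version 9 of April 5th, 2024, which is not shown and may carry a full list of criteria and a procedure for deaths. That possibility stands, and it determines what has to be corrected. It does not remove the point: the article does not leave the definition to another document but states one, and the stated one misclassifies these events.

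Second, the events are not lost. All untoward events go into REDCap and falls are counted separately. This stands. A disabling fall without admission would still be recorded; its label and its speed of reporting would differ. A reader might infer that such events vanish from the safety data, and the text does not support that.

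Third, site ethics rules may require prompt reporting. They may, but the article invokes them for serious events, alongside the DSMB report. A report to a local ethics board is not a report to the DSMB.

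Fourth, many life-threatening events and disabling falls would lead to admission and so already qualify. This is likely, and it limits the gap mainly to deaths outside hospital and events handled without admission.

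Three stronger readings are tempting but go beyond the documents:
- A reader might infer that such an event will reach the DSMB 4 months late. That requires a death or disabling injury to be filed as minor, which the article does not say.
- A reader might put the effect on the serious-event rate at 2 to 4 percentage points. With 50 per group, that is only 1/50 = 2% and 2/50 = 4% for hypothetical events, not an estimate.
- A reader might add that elective admissions are wrongly counted as serious. This is weak, because the monitoring section limits adverse events to untoward ones.

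**Conclusion.** The point holds in a limited form. As worded, a death outside hospital, or a life-threatening or disabling event managed without admission, is not a serious adverse event. It has no stated expedited route to the DSMB and does not enter the serious-event count. It could reach the DSMB as late as the 4-monthly report if filed as minor; otherwise its route is simply unstated. The documents give no rate for deaths, serious events or non-admitted injuries, so no size can be put on the effect.

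The conclusion assumes that the article's sentence is the rule sites apply. If version 9 is broader, the fault is confined to the article's wording. The documents do not show that any event has been or will be missed.

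**What to change.** Extend the definition in Secondary outcomes so that a serious adverse event includes death, a life-threatening event and persistent or significant disability, alongside admission to acute care. In Data collection and monitoring, send all of these through the existing 48-hour DSMB report, so that every event that is not minor has a stated route. Re-code the adverse events already logged against the wider definition before the safety results are tabulated.

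The cost is modest but real. The amendment must pass through sites in five provinces, with site-specific ethics processes. The re-coding covers at least the 57 participants randomized by July 15th, 2025 (Trial Status). A few more expedited reports would follow. Intervention, sample size and primary analysis are unchanged. If version 9 already defines the term this way, no amendment is needed and the article should be corrected to match.
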